#### Parent measures

I.Participant characteristicsParent’s demographic questionnaire will assess ethnic background, family composition, parent(s) education and parent(s) occupation. Date of the child’s T1DM diagnosis, insulin delivery method and method of glucose monitoring will also be collectedII.Fear of hypoglycaemiaParental fear of hypoglycaemia will be assessed using the Parent Hypoglycemia Fear Survey (PHFS) [50]. The PHFS is comprised of a 10-item behaviour (B) subscale and a 15-item worry (W) subscale. Higher scores indicate greater fear of hypoglycaemia. This scale is the same as the children’s version, the only difference is that it asks about parental fear of hypoglycaemia. Research shows that the PHFS can provide reliable self-report of parental fear of hypoglycaemia [50]. It also asks parents to report the number of severe hypoglycaemic episodes that their child has experienced in the past 12 monthsIII.Child health-related quality of lifeThis 28-item questionnaire (CHQ-PF28) assesses physical and psychosocial wellbeing of the child, from parent perspective, and can be used as a proxy quality of life measure for health-utility [54]. Higher scores indicate better health-related quality of life. The CHQ-PF28 has demonstrated reliability and validity in parents of children aged 4–13 years [54]IV.Additional self-reported itemsAdditional items self-reported by parents (‘follow-up questionnaire’) will include: (1) number of additional contacts with the diabetes team other than routine clinic visits in the last 6 months, (2) number of hospital admissions other than routine clinic visits in the last 6 months, (3) days off school in the last 6 months, (4) additional medications in the last 6 months and (5) perceived frequency of communication about physical activity in consultations with the diabetes health care team

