#### Outcome measures

Outcome measures will be completed at baseline (T0), 8 weeks (T1) and 6 months (T2).

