### Secondary outcome measures

The following standardised measures have adequate psychometric properties and have been used in other studies with children of the same age range who have T1DM [22] or other long-term conditions [21]. Our previous research [22] and significant patient and public involvement activities have indicated that the assessments may take approximately 45–60 min to complete. The outcomes measured at T0, T1 and T2 will be:

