#### Child measures

I.Self-reported physical activitySelf-reported frequency of different types of physical and sedentary activities will be assessed with a 55-item physical activity questionnaire (PAQ) [46] adapted from the full 80-item PAQ [47]. The questionnaire refers to the previous 24 h and children are asked to rate a range of activities, on a three-point scale (none, a little, a lot) at three time points (yesterday afternoon, last night, this morning). Higher scores indicate greater frequency of engagement in physical activity. The authors of the PAQ reported good agreement between questionnaire responses for PAQ and observed activities [47]. Furthermore, combining interview technique with probing activity in the recent past is considered most likely to generate results that correlate with objective measures of activity [48]. The 55-item PAQ has been found to discriminate physical activity levels in children attending paediatric outpatient clinics [46]II.Self-efficacy for physical activityChildren’s self-efficacy for physical activity will be measured using the Children’s Self-Perceptions of Adequacy in, and Predilection for, Physical Activity scale (CSAPPA) [49]. CSAPPA is a 20-item scale to measure the self-perception of confidence in, preference for, and enjoyment of physical activity. CSAPPA is composed of three subscales: (1) perceived adequacy (perceived ability to achieve some level of successful with respect to being physically active), (2) predilection toward physical activity (preference for being active over being sedentary when given the choice) and (3) enjoyment of physical education class. The scale employs a structured alternative choice format. Children are asked to choose the option that best describes them from pairs of statements about other children such as, ‘Some kids can’t wait to play active games after school’ and ‘Other kids would rather do something else’ by indicating whether the sentence was either ‘sort of true for me’ or ‘really true for me’. Higher scores for subscales indicate greater perceived adequacy, predilection for, and enjoyment of physical activity. The scale was designed by Hay (1992) [49] for 9–16 year-olds and has demonstrated high test-retest reliability and strong predictive and construct validityIII.Fear of hypoglycaemiaChildren’s fear of hypoglycaemia will be assessed using the Child Hypoglycemia Fear Survey (CHFS) [50]. CHFS is comprised of a 10-item behaviour (B) subscale and a 15-item worry (W) subscale. HFS-B items describe behaviours performed in order to avoid hypoglycaemic episodes and/or their negative consequences (e.g. by limiting exercise or physical activity). HFS-W items ask about specific concerns about hypoglycaemic episodes (e.g. episodes occurring during sleep, or having an accident). Higher scores indicate greater fear of hypoglycaemia. Previous research has indicated that the children’s HFS is a valid and reliable measure of youth fear of hypoglycaemia and that it significantly correlated with other measures of anxiety [50]IV.Health-related quality of lifeChild Health Utility 9D (CHU9D) [51] is a health-related quality of life measure for children aged 7–17 years, which allows the calculation of quality-adjusted life years (QALYs) for use in cost-utility analysis. It consists of nine items (worry, sadness, pain, tiredness, annoyance, school, sleep, daily routine and activities) each represented by a single question with five response options (scored 1–5). Higher scores indicate better health-related quality of life. The recall period is today/last night. The CHU9D has demonstrated validity in paediatric clinical populations [52]V.Communication questionnaireA short questionnaire developed specifically for this study will be used to explore children’s perceptions of the communication around physical activity they have with their diabetes team. It contains two items and assesses children’s perceptions of (1) frequency of physical activity discussion (e.g. ‘In the last 6 months, have you spoken to one of your diabetes doctors or nurses about physical activity, exercise or sport?’ and, ‘If yes, how many times (1–5+)?’) and (2) difficulty of physical activity discussions (e.g. ‘talking to your diabetes doctors and nurses about physical activity, exercise or sport is…..?’ (5-point scale; really hard to really easy))VI.Objective physical activityPhysical activity will be measured objectively using a PolarActive wrist-worn activity watch (Polar Electro Inc., Lake Success, NY, USA) at T0, T1 and T2 in intervention and control group children. Wrist-worn activity monitors have demonstrated acceptability and feasibility among children with T1DM in previous research [22]. The PolarActive device has shown to be preferred by children aged 7–10 years compared with other devices, and is associated with the highest level of compliance [53]. Children will be given the PolarActive watch for 7 days at each time point, and start date (day of the week) will vary according to recruitment date; we will monitor patterns of physical activity over the data collection period. Day 1 will be considered as a familiarisation day to minimise potential reactivity and data will be analysed if activity watches are worn for at least 600 min on at least 3 days. Physical activity will be measured as step counts and average minutes in moderate-to-vigorous physical activity per dayVII.Clinical outcome measuresThese measures are routinely collected by the diabetes health care team and, with consent, will be taken from the child’s clinic notes. The measurement that coincides most accurately with the data collection period (T0, T1 and T2) will be taken.

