### Data collection, management and analysis

#### Data collection methods

Participants will have six visits for data collection. Visits will take place at either the child’s usual paediatric diabetes clinic or another mutually convenient location (e.g. the participants’ home) depending on parent preference, and preferred locations for data collection will be recorded. Children and parents will complete the assessments at visits 1 (baseline/T0), 3 (T2) and 5 (T3). Children will be assessed for self-reported physical activity (PAQ), self-efficacy for physical activity (CSAPPA scale), fear of hypoglycaemia (CHFS), health-related quality of life (CHU9D), clinician-patient communication and objective physical activity (PolarActive). As close to visits 1, 3 and 5 as possible, the researcher will ask the clinician for clinical data from the participants’ clinical records (height, weight, HbA1c level and insulin dosage). Parents will be assessed for demographics, fear of hypoglycaemia (PHFS), child’s quality of life (CHQ-PF28) and additional self-reported items. One week after visits 1, 3 and 5 (at visits 2, 4 and 6), data from the activity watch will be downloaded. Health care professionals drawn from the paediatric diabetes teams at the study sites will be asked to complete a clinician-patient communication questionnaire at T0, T1 and T2.

At visit six, all child-parent dyads in the intervention group will be invited to participate in single exploratory interview as part of the process evaluation. All participant dyads who have dropped out of the study will be invited to interview (at the point when they leave the study). For practical reasons child and parent will be interviewed together with questions/topics directed to each as appropriate. Interviews will be undertaken face-to-face at a time and venue convenient to the family.

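### As the article reads, 6- and 12-month recall items are asked at the 8-week visit, where 69% and 85% of their windows precede randomisation; the 12-month item is still half pre-randomisation at 6 months

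*Protocol article*

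**What the plan says.** Timing. The Outcome measures section states "Outcome measures will be completed at baseline (T0), 8 weeks (T1) and 6 months (T2"; the Secondary outcome measures section opens its list of child and parent measures with "The outcomes measured at T0, T1 and T2 will be". Data collection methods says "Children and parents will complete the assessments at visits 1 (baseline/T0), 3 (T2) and 5 (T3". The visit labels there differ from the rest of the article, but visit 3 is plainly the 8-week visit. That section counts the parent fear survey, the "child’s quality of life (CHQ-PF28) and additional self-reported items" and the child communication questionnaire among the assessments, and ties none of them to a single visit. The Recruitment section puts randomisation after baseline data collection.

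Recall. Under Parent measures, the additional items are "number of additional contacts with the diabetes team other than routine clinic visits in the last 6 months", "number of hospital admissions other than routine clinic visits in the last 6 months" and "days off school in the last 6 months, (4) additional medications in the last 6 months". A fifth item, on perceived frequency of communication, states no recall period. The parent fear survey also collects a count of severe hypoglycaemic episodes over 12 months. Under Child measures, the communication questionnaire gives as an example "In the last 6 months, have you spoken to one of your diabetes doctors or nurses about physical activity".

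No shorter recall period for the 8-week visit is stated.

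**The concern.** A recall question measures follow-up only if its window starts at or after randomisation. A 6-month question asked at 8 weeks mostly describes life before the trial, and a 12-month question does so even more. Pre-randomisation events have the same expectation in both arms, so they pull any contrast between arms towards no difference.

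This matters in a feasibility trial because one of the main objectives (number 6) is to test the collection of health, clinical and economic measures for the larger trial, and the Health care costs section plans a retrospective estimate of resource use. A form whose window does not fit the visit could pass the 70% completion criterion and be carried into the definitive trial without measuring the intended period.

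Eligibility adds a smaller problem. A child may enter 3 months (about 13 weeks) after diagnosis. The 6-month window at T1 reaches back 18 weeks before baseline, about 5 weeks beyond that diagnosis. Contacts and admissions around diagnosis would then be reported at the 8-week visit.

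**Working it through.** The plan gives no figure of its own on this point, so there is nothing to reproduce. The check is interval arithmetic.

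Inputs:
- Randomisation at week 0 (Recruitment).
- T1 at t = 8 weeks and T2 at 6 months, taken as t = 26 weeks (Outcome measures).
- Recall length L = 26 weeks for contacts, admissions, school absence, medications and the child communication item; L = 52 weeks for severe hypoglycaemia.

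The window at visit t runs from t − L to t. Its pre-randomisation share is max(0, L − t)/L.

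| Item | Visit | Window (weeks) | Pre-randomisation share |
|---|---|---|---|
| 6-month | T1 | −18 to 8 | 18/26 = 69% |
| 6-month | T2 | 0 to 26 | 0/26 = 0% |
| 12-month | T1 | −44 to 8 | 44/52 = 85% |
| 12-month | T2 | −26 to 26 | 26/52 = 50% |

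Using 26.09 weeks for 6 months moves no share by more than 0.2 percentage points.

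Overlap of the T1 and T2 windows: 8 weeks for the 6-month items (weeks 0 to 8, all the post-randomisation time that T1 contains) and 8 − (−26) = 34 weeks for the 12-month item.

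Dilution, for illustration. Assume a constant event rate before randomisation and in controls, and a true rate ratio R after randomisation. With pre-randomisation share p, the expected ratio of counts is p + (1 − p)R.
- R = 2: (18 + 16)/26 = 1.31 for 6-month items at T1; (44 + 16)/52 = 1.15 for the 12-month item at T1; (26 + 52)/52 = 1.50 for the 12-month item at T2.
- R = 0.5 to 0.8: 0.85 to 0.94, 0.92 to 0.97 and 0.75 to 0.90 respectively.

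Subtracting visits does not recover the missing period. For a 6-month item, T1 minus T0 equals events in weeks 0 to 8 minus events in weeks −26 to −18. For the 12-month item, T2 minus T1 equals events in weeks 8 to 26 minus events in weeks −44 to −26. One count per window cannot separate the two parts.

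If the 6-month answers at T1 and T2 were added, they would span 52 reported weeks for 26 weeks of follow-up: weeks 0 to 8 twice, plus 18 weeks before the trial.

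**The case against.** The strongest objection is to the premise. Table 2, which sets out assessments by time point, is not shown. The general statements cannot be a strict item schedule, since read literally they have parents repeat demographics at every visit. The article also labels the additional parent items a follow-up questionnaire and often uses follow-up for the 6-month visit; a 6-month recall suits a T0 and T2 schedule exactly. This stands as a real doubt about the 6-month parent items. It is not decisive, because T1 is also a follow-up visit and nothing shown excludes these items from it. It also leaves the 12-month item at T2 untouched unless that item is asked at baseline only.

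Stronger readings that a reader might infer are not supported:
- That health service use after randomisation cannot be measured at all. At T2 the 6-month items cover exactly the post-randomisation period.
- That resource use will be double-counted. No section says T1 and T2 are summed; the overlap does harm only if they are.
- That the parent communication item shares the fault. It states no window.
- That the main safety comparison is masked. The Adverse events text identifies hypoglycaemic episodes from meter and pump downloads, and the Harms section records onset dates. The parent count accompanies a fear survey. It keeps some value, because the article defines a severe episode by another person's help and a glucose record alone does not show that.

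The objection that these are secondary measures in a small feasibility trial limits the weight of the point but does not remove it, given the objective of testing data collection.

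**Conclusion.** The point holds on the text shown. At the 8-week visit, 69% of the window of the 6-month items (contacts, admissions, school absence, medications, child communication) and 85% of the window of the 12-month severe-hypoglycaemia item lie before randomisation. At 6 months the 12-month item is still 50% pre-randomisation, while the 6-month items are sound.

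Assumptions: visits fall at their nominal times; the general timing statements apply to these items, which Table 2 could qualify; and the child item, quoted as an example, is worded as shown. The percentages are shares of time and equal shares of events only if the event rate is constant.

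The change is worth making because it is cheap and serves a main objective, but it does not threaten the trial's feasibility conclusions.

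**What to change.** First confirm from Table 2 which visits use the 6-month parent items. Then:
- **T0:** keep the 6- and 12-month wording.
- **T1:** ask the 6-month items and the severe-hypoglycaemia count about the time since joining the study, or omit the 6-month items at this visit.
- **T2:** keep the 6-month wording, or its equivalent, time since joining the study. Ask severe hypoglycaemia since joining the study instead of over 12 months.
- **Costing:** take post-randomisation resource use from the T2 answer alone and do not add T1.

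With these changes the pre-randomisation share is 0% at both follow-up visits. The T2 items should not be changed to ask about the time since the previous visit: the 26-week total would then depend on attending T1, and the plan accepts retention as low as 70% at each time point.

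The cost is a few reworded questions. The severe-episode count is described apart from the fear survey's behaviour and worry subscales, so their scoring is unaffected. Recruitment was already under way, so at most 50 dyads would have mixed versions; answers given under the old wording should be flagged and reported separately.

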#### HCP measures

I.Clinician-patient communicationA nine-item clinician-patient communication questionnaire has been developed specifically for this study and will be used to explore HCPs’ perceptions of the communication around physical activity they have with their patients. It aims to assess (1) how often clinicians have discussed physical activity with their patients and (2) how clinicians feel about talking about physical activity based on how much they agree with statements (e.g. ‘I am able to talk to children and their parents about physical activity.’)

#### Participant timeline

Figure 1 shows a flow chart of study processes. Table 2 shows the assessments at each time point.

**Fig. 1 Fig1:**
[figure not shown]
Flow diagram of the study. *CHFS* Child Hypoglycaemia Fear Survey, *CHQ C*hild Health Questionnaire, *CHU9D* Child Health Utility Instrument, *CSAPPA* Children’s Self-Perceptions of Adequacy in, and Predilection for, Physical Activity scale, *HCP* health care professional, *PAQ* Physical Activity Questionnaire, *PHFS* Parent Hypoglycaemia Fear Survey, *Q* questionnaire, *RCT* randomised controlled trial, *STAK-D* Steps to Active Kids with Diabetes

**Table 2 Tab2:**
[figure not shown]
Study assessments at specific time points

### Sample size

The sample size will be adequate to estimate the critical parameters (e.g. recruitment rate) to the necessary degree of precision and to provide key information on the feasibility of the intervention. There are approximately 170 patients in the specified age range across both recruitment sites, prior to exclusions. We will target the recruitment of 50 child-parent dyads (approximately five per month over 9–10 months). We envisage this to be achievable since previous studies indicate a 40–50% response rate with similar populations [22, 55] and our selected feasibility study sites currently have recruitment rates exceeding 100% for NIHR-adopted studies. Recruitment of a minimum of 33 child-parent dyads (40%) would be deemed necessary to progress to full trial; should recruitment be problematic a remedial act will be to revise inclusion criteria to include age range 8–13 years. At T2, up to 25 child-parent dyads and up to 10 HCPs will take part in interviews.

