#### Primary outcome measures

The primary outcome measures for the feasibility study are as follows:Recruitment rateAn estimate of the number of eligible patients and likely uptake rate will be assessed. The response rate for mailed invitation will be compared to clinic (face-to-face) recruitment rates. Refusal rate and reasons for nonparticipation will be assessed. This will enable a prediction of recruitment rate, number of sites and length of time needed to recruit the required number of patients for a future trial. A recruitment rate of between 25 and 40% would be considered reasonable based on our previous research [22] and similar studies [44, 45]Adherence ratePattern of intervention use will be monitored to assess fidelity of intervention delivery. We will explore users’ activity by website and page visits, more or less commonly used elements, and engagement with goal-setting and activity tracking. We will assess user satisfaction with STAK-D (e.g. navigation, ease of use, technical issues) at 6 months. Acceptable compliance will be defined as the child using the online resources and tracking their daily activity (using the PolarActive watch). Noncompliance will be defined as the child’s failure to access the STAK-D website and track their physical activity over the intervention periodRetention rateRetention will be defined as the number of participants completing the STAK-D programme including all scheduled follow-up data collection (T0, T1 and T2) compared to the number started. A retention rate of at least 70% at each time point would be considered feasible based on our previous research [22] and similar studies [44, 45]Data completion rateCompletion of outcome measures will be recorded at T0, T1 and T2 (complete and partial or noncompletion with reasons, including time to complete). Measures will be determined acceptable to parents and children (in terms of literacy, cognitive ability and capacity to understand) if more than 70% are fully completed (indicating quality data), and reported participant burden is minimal.The feasibility of gathering routinely collected clinic data from patients’ electronic diabetes record (height, weight, HbA1c level and insulin dosage) at T0, T1 and T2 will be assessed. This will allow us to ascertain the proportion of our sample with complete clinical records, and whether records will be accessible to our researchers at specified data collection time points. Feasibility of collecting observational data in this way will be determined if more than 85% of the sample have complete clinical records availableAdverse eventsAny adverse events experienced as a result of participation in the intervention will be recorded and evaluated. Adverse events are defined as any serious negative outcome resulting from the physical activity undertaken as part of the STAK-D programme. Severe hypoglycaemia, i.e., a blood glucose level below 4 mmol/l requiring the help of another person to treat it, will be considered an adverse event in either group. Data from meter and pump downloads combined (and meter downloads alone for those patients not on insulin pump therapy) will be used for identification of hypoglycaemic episodes, as per usual care at our participating sites. To determine the likelihood of adverse events being associated with the physical activity undertaken as part of the STAK-D programme, we will record whether the frequency and/or severity of hypoglycaemic episodes increased during the intervention period. The occurrence of adverse events related to the intervention will be assessed and compared to the control group (see ‘Harms’ section for potential adverse events).

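### The progression minimum of 33 dyads (40%) fits no base the protocol states, and its 40% is the top of the range called reasonable under the primary outcomes

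*Protocol article*

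**What the plan says.** Two places in the protocol article set a standard for recruitment.

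- **Sample size.** The progression threshold is "Recruitment of a minimum of 33 child-parent dyads (40%) would be deemed necessary to progress to full trial". The same paragraph describes the pool ("There are approximately 170 patients in the specified age range across both recruitment sites, prior to exclusions") and the target ("We will target the recruitment of 50 child-parent dyads (approximately five per month over 9–10 months"). It supports the target by noting that "previous studies indicate a 40–50% response rate with similar populations". It adds that "should recruitment be problematic a remedial act will be to revise inclusion criteria to include age range 8–13 years".
- **Primary outcome measures, recruitment rate.** "A recruitment rate of between 25 and 40% would be considered reasonable based on our previous research". No denominator is fixed for this rate, and the number of eligible patients is listed as something the study will estimate.

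No sentence links the 25 to 40% range to the minimum of 33 dyads.

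**The concern.** The main aim is to decide whether a definitive trial is feasible, and recruitment rate is the first primary outcome. The minimum of 33 dyads is the only numerical criterion the article explicitly calls necessary for progressing, so it should give one answer for one result. It has two weaknesses.

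First, the count and the percentage are printed as equivalent, but they are equivalent only on a base the article does not give. Whoever applies the rule must choose between them, or choose a denominator, possibly with the recruitment figures already known.

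Second, 40% is the lowest acceptable rate in one section and the upper end of the reasonable range in the other. A recruitment rate of, say, 30% could be reported as in line with expectations and also as short of what progression requires.

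**Working it through.** **Inputs, all from the protocol article.** Minimum 33 dyads, labelled 40%; pool about 170 before exclusions; target 50 dyads; cited response rate 40–50% (all Sample size). Reasonable range 25–40% (Primary outcome measures). The number eligible after exclusions is not given, so values from 82.5 to 170 are used below as assumptions, plus one smaller value for illustration.

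**Step 1. Try to reproduce 33 = 40%.**

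| Base | 33 ÷ base | 40% of base |
|---|---|---|
| 170 (pool) | 19.4% | 68, more than the target of 50 |
| 50 (target) | 66% | 20 |

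Neither base reproduces the figure. Working backwards, 33 ÷ 0.40 = 82.5. Only two whole-number bases round to 40%: 33 ÷ 82 = 40.2% and 33 ÷ 83 = 39.8%. Reaching 82.5 from 170 means that 1 − 82.5/170 = 51% of the pool is excluded or not approached, which the article does not say.

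One two-step construction comes close: 50% of 170 = 85 responders, and 40% of 85 = 34. But 33 ÷ 85 = 38.8%, and the article describes no such step. With 40% or 45% responding, the same product gives 27.2 or 30.6.

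**Step 2. See how count and percentage behave on other bases.**

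| Assumed base | 33 as % | 25% of base | 40% of base | 50 as % |
|---|---|---|---|---|
| 82.5 | 40.0 | 20.6 | 33 | 60.6 |
| 100 | 33.0 | 25 | 40 | 50.0 |
| 120 | 27.5 | 30 | 48 | 41.7 |
| 150 | 22.0 | 37.5 | 60 | 33.3 |
| 170 | 19.4 | 42.5 | 68 | 29.4 |

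On 120, recruiting 33 to 47 dyads meets the count and fails the percentage. On a base below 82 the disagreement reverses: with an assumed 70, 40% is 0.40 × 70 = 28, so 28 to 32 dyads meets the percentage and fails the count.

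**Step 3. Compare with the reasonable range.**

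- On 82.5, 25% is 20.6, so 21 to 32 dyads is reasonable in one section and below the minimum in the other.
- Since 33 ÷ 0.25 = 132, on any base above 132 a result of exactly 33 dyads meets the count but falls below the 25% floor. On 170 it is 19.4%.
- On 170, full recruitment of 50 (29.4%) is reasonable but would not reach 40%.

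**Step 4. Put the target on the same base.** 50 ÷ 170 = 29.4%. 50 ÷ 83 = 60.2%. If 83 means dyads approached, the cited 40–50% would yield 0.40 × 83 = 33 to 0.50 × 83 = 42 dyads, short of 50.

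**The case against.** The best defence is that no arithmetic error has been shown. The 170 is explicitly a figure before exclusions, so a base of 82 or 83 after exclusions is compatible with the text, and the fuller protocol or the flow diagram, neither available here, may give it. That stands. A reader might infer that 33 is simply wrong, and the article does not support that.

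Next, the threshold leads with a count and puts the percentage in brackets. Read as a count, it needs no denominator. This is a fair reading, but the article does not say that the count governs, and the bracketed figure is the only one comparable with the range under the primary outcomes.

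Third, a reader might infer that one result is formally both a go and a stop. The text does not go that far. The 25 to 40% range is described as reasonable, not as a criterion for progressing; neither section uses the word stop; and a rate can be reasonable without being enough. What remains is an unexplained tension between the benchmark for a primary outcome and the progression threshold.

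Fourth, it is tempting to say that the target of 50 contradicts the cited response rate. That holds only if 83 means dyads approached. The Recruitment section describes a postal expression of interest followed by consent at a clinic meeting. If 83 were responders (48.8% of 170, within the cited 40–50%), then 50 ÷ 83 would be consent among responders and could not be compared with a response rate.

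The planned widening of the age range does not settle the matter, because it changes the denominator as well.

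**Conclusion.** The point holds as a defect in a stated decision threshold and should be fixed. The 40% cannot be reproduced from either base the article gives (19.4% of 170; 66% of 50), and it agrees with 33 only on 82 or 83. On other bases the count and the percentage can give opposite answers. Separately, every rate from 25% to just under 40% is reasonable under the primary outcomes and insufficient under Sample size.

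The two stated bases need no assumption; the figures for 82.5, 100, 120, 150 and 70 are illustrations, because the eligible number is unknown. Nothing here affects participant safety, randomisation, data collection or any effect estimate. Feasibility as defined under Aim also rests on identification, retention and acceptability, so this is a clarification of one criterion, though the one that most directly governs progression.

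**What to change.** Before recruitment results are reviewed:

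1. Define the recruitment rate once. The numerator would be dyads randomised, with a single named denominator, such as eligible dyads approached, and its expected size.
2. Say whether the count or the percentage is the operative rule, and correct the other to match on that denominator.
3. Replace the statements under Sample size and Primary outcome measures with one rule. An option using the protocol's own figures is to proceed at 40% or more, and at 25% to under 40% to proceed only after the recruitment plan is amended. This middle band is a suggestion and is not in the article; the sponsor may choose another single rule.
4. Restate the target of 50 on the same denominator: 29% if the base is 170; about 60% if it is 83 dyads approached, in which case the supporting 40–50% response rate also needs revisiting.
5. Say how the denominator is counted if the age range is widened.

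The cost is a wording amendment with no extra participants. The restated figures may look slightly less favourable. The Trial status section reports recruitment as ongoing, so at that stage the rule could still be settled ahead of the results.
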